### Statistical analysis

Data analyses will follow an intention-to-treat approach using multilevel models implemented in R (‘lme4’ or ‘glmer’ packages). This approach accounts for the nested structure of repeated measures within participants and participants nested within centres. Model assumptions will be assessed using scatter plots of residuals and Quantile-Quantile (QQ) plots. Multilevel models are generally robust to moderate violations of normality. Models will be estimated using maximum likelihood, which uses all available data under a missing-at-random assumption.

We will build separate multilevel models for each primary and secondary outcome. Timepoint will be included as a categorical within-subject variable with four levels (T0 = baseline; T1 = pre-intervention; T2 = post-intervention; T3 = follow-up). Centre and tDCS condition (active vs. sham) will be included as between-subject variables. Given the staged recruitment, cohort will be included as a fixed-effect covariate to account for cohort-related differences over time (e.g., staff changes or evolving site practices). Models will include a random intercept for baseline differences across individuals, and, where supported, a random slope for timepoint will allow individual trajectories over time (simplified if convergence issues arise). Fixed effects will be estimated for timepoint, tDCS condition, centre, cohort, and their relevant interactions. We will set T1 (pre-intervention) as the reference level to be able to compare T0 vs. T1 (changes during waitlist period), T2 vs. T1 (changes during intervention), and T3 vs. T1 (longer-term changes).

The primary CR effect will be evaluated by comparing changes observed during the intervention period with changes during the waitlist period, pooling across tDCS conditions. The tDCS augmentation hypothesis will be tested via the intervention × timepoint interaction, operationalised as the difference in change from T1 to T2 and from T1 to T3 between active tDCS and sham tDCS. Given the trial is powered for the primary within-subject CR effect rather than the between-group tDCS contrast, tDCS results will be interpreted as secondary and hypothesis-generating, emphasising effect size estimates and 95% confidence intervals.

We have three primary outcomes (GAS, ILSS-O, ILSS-SR). To control multiplicity, we will control the family-wise Type I error rate across the three primary outcomes at two-sided α = 0.05 using the Holm correction.

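### Fixing maximum likelihood for the final models makes standard errors about 1% to 4% too small, so the Holm family-wise error can modestly exceed 5%; REML would avoid this

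*Protocol article*

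**What the plan says.** The Statistical analysis section fixes the estimator: "Models will be estimated using maximum likelihood, which uses all available data under a missing-at-random assumption". No other reason for ML is given, and REML is not mentioned.

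The fixed part of the model is potentially large: "Fixed effects will be estimated for timepoint, tDCS condition, centre, cohort, and their relevant interactions". The article does not list which interactions count as relevant. The random part is described thus: "Models will include a random intercept for baseline differences across individuals, and, where supported, a random slope for timepoint". The primary effect of cognitive remediation (CR) is a within-person contrast, obtained by "comparing changes observed during the intervention period with changes during the waitlist period, pooling across tDCS conditions".

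The error-rate claim is explicit: "we will control the family-wise Type I error rate across the three primary outcomes at two-sided α = 0.05 using the Holm correction". The outcomes are the GAS and the informant and self-report versions of the ILSS. The section names no test statistic, reference distribution or degrees-of-freedom method.

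**The concern.** ML divides the residual sum of squares by the number of observations without deducting what was spent on fixed effects. Variance components, and hence standard errors, come out too small. REML makes that deduction. The size of the bias depends on how many fixed effects act on the contrast of interest. The open-ended set of interactions matters here, because cohort is meant to absorb differences over time, which may imply cohort-by-timepoint terms.

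The reason given does not favour ML. REML is also likelihood-based, uses the same incomplete records and rests on the same missing-at-random assumption.

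If nothing changes, the p-values passed to Holm are slightly too small and the 95% confidence intervals slightly too narrow, for the CR effect and for the tDCS contrast alike. This is a stated choice, so an analysis plan that follows the article would carry it forward.

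**Working it through.** **Inputs from the article**
- N: 126 recruited with 20% dropout (sample size section). 126 × 0.8 = 100.8, so I use N = 100 and N = 126.
- Four timepoints, so three within-person contrasts and m = 3N within-person degrees of freedom before fixed effects.
- tDCS has 2 levels, centre 3 and cohort 5.
- α = 0.05 two-sided, Holm over 3 outcomes: the smallest p-value is tested at 0.05/3 = 0.0167.

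**Assumptions not in the article**
- Complete balanced data and normal errors.
- For the base case, a random intercept with one common residual variance.
- Correlation between outcomes of 0 to 0.5.

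**Time-related fixed effects, p**
- Timepoint and timepoint × tDCS only: 3 + 3 = 6, or 2 per contrast.
- Adding timepoint × centre (3 × 2 = 6) and timepoint × cohort (3 × 4 = 12): 6 + 6 + 12 = 24, or 8 per contrast.

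**Standard-error ratio**

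SE(ML)/SE(REML) = √((3N − p)/(3N)).
- N = 100, p = 6: √(294/300) = 0.990
- N = 126, p = 6: √(372/378) = 0.992
- N = 100, p = 24: √(276/300) = 0.959
- N = 126, p = 24: √(354/378) = 0.968

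A variance specific to the primary contrast gives the same ratio, because 2/N = 6/(3N) and 8/N = 24/(3N). Only the degrees of freedom change, from 3N − p to N − 2 or N − 8.

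**Actual size of a nominal two-sided 5% test under ML**

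Size = 2 × P(t_ν > c × ratio), where ν is the residual degrees of freedom and c is the t or z critical value.

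| N | Timepoint interacts with | t reference | z, common variance | z, contrast-specific variance |
|---|---|---|---|---|
| 100 | tDCS | 5.2% | 5.3% | 5.5% |
| 126 | tDCS | 5.2% | 5.3% | 5.4% |
| 100 | tDCS, centre, cohort | 6.0% | 6.1% | 6.3% |
| 126 | tDCS, centre, cohort | 5.8% | 5.9% | 6.0% |

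The t column is the part due to ML alone. REML with z gives 5.1% (common variance) or 5.2% to 5.3% (contrast-specific). At N = 100 with contrast-specific variance:
- Simple model: ML with z 5.52%, ML with t 5.23%. More than half of the small excess comes from z.
- Rich model: ML with z 6.33%, ML with t 5.99%. ML accounts for 0.99 of the 1.33 points.

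**Holm family-wise error, all three nulls true**

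For independent outcomes this is 1 − (1 − a)³, where a is the actual size at the first step. A correctly sized test gives 1 − (1 − 0.0167)³ = 4.9%, which is also the result for REML with t. For correlated outcomes, 60,000 simulated trials per setting were used (simulation standard error √(0.05 × 0.95/60,000) ≈ 0.1 percentage point).

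| Setting, common variance, N = 100 to 126 | Independent | Correlation 0.5 |
|---|---|---|
| ML with z, p = 6 | 5.3% to 5.4% | 4.7% to 4.8% |
| ML with z, p = 24 | 6.2% to 6.6% | 5.7% to 5.9% |

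REML with t gives 4.4% to 4.8% at correlations of 0.3 to 0.5. As a sensitivity check, contrast-specific variance with z and independent outcomes gives 5.6% to 5.8% (simple model) and 6.5% to 7.0% (rich model).

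**The case against.** ML is a legitimate estimator, and the sentence about missing data is true as it stands; it does not claim superiority over REML. With 100 or more participants and few interactions, the two estimators differ by about 1% in the standard error. The test and degrees-of-freedom method are details that an analysis plan commonly settles, so their absence from an article is not a fault, and any figure based on z tests rests on an assumption. The richest model is one reading of the interactions, not a stated choice. The tDCS contrast lies outside the Holm family and is declared hypothesis-generating. REML is not available for glmer fits, which the article allows and which may be needed for the Behapp counts.

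All of this limits the size and reach of the point. What it does not answer is that the article names ML for final inference, gives a reason that applies equally to REML, and promises a family-wise 5%.

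A reader might infer that ML breaks the Holm guarantee. The documents do not support that. Two of the three primary outcomes are versions of one instrument, so some correlation is plausible. With correlation 0.5 and only tDCS interacting with timepoint, family-wise error stays below 5% even under ML with z tests. A reader might also reach larger excesses by assuming fewer completers, but the article's own recruitment and dropout figures give about 100.

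**Conclusion.** The point holds as a small and avoidable anticonservatism. From ML alone, standard errors are about 1% too small in the simplest model and 3% to 4% too small in the richest, and a nominal 5% test runs at about 5.2% to 6.0%. If z tests are also used, the range is about 5.3% to 6.3%. Family-wise error is about 4.7% to 6.6% under a common residual variance and a z reference. Where it falls depends on the interactions fitted and the correlation between outcomes, neither of which the article gives. It can exceed 5%, but a breach is not established. The figures assume complete, balanced, normally distributed data at N = 100 to 126. For the tDCS contrast the only consequence is slightly narrow intervals. The conclusions of the trial would change only if a primary result fell close to its Holm threshold.

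**What to change.** State that the final linear mixed models are fitted by REML, with tests and 95% confidence intervals based on Satterthwaite or Kenward-Roger degrees of freedom. Keep ML for likelihood-ratio comparison of fixed-effect structures and for generalised models fitted with glmer, where lme4 offers no REML option. Both parts are needed: REML with z tests leaves a small excess for a single test, and ML with t tests leaves most of the excess in a rich model.

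The cost is a sentence in the analysis text and a software option. Data and missing-data assumption are unchanged. Intervals widen by about 1% in the simple model (1/0.990 = 1.010) and about 4% in the richest at N = 100 (1/0.959 = 1.043), apart from the slightly larger t critical value. Recruitment is still under way, so the change can be made before unblinding.

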## Method

### Trial design

This pragmatic, triple-blinded, randomised, sham-controlled multi-centre trial follows a non-concurrent multiple baseline design (Fig. 1). Recruitment and eligibility assessment are followed by enrolment into five cohorts, each comprising approximately 20–24 participants, spaced 16–20 weeks apart. After inclusion, participants complete two baseline assessments (T0, T1), separated by a 16-week waiting period serving as a within-subject control, offering greater internal validity than a between-subject design. This design enables all participants to receive the intervention and attain its potential benefits. After T1, participants are randomised to either CR + active tDCS or CR + sham tDCS. After the 16-20-week intervention period, outcomes are reassessed post-treatment (T2, within 2 weeks) and at 6-month follow-up (T3).

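### The cohort covariate cannot account for changes over time in the primary CR contrast: it is constant within a participant and cancels

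*Protocol article*

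**What the plan says.** All references are to the protocol article.

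- **Contrast.** Under Statistical analysis: "The primary CR effect will be evaluated by comparing changes observed during the intervention period with changes during the waitlist period, pooling across tDCS conditions". Write this as (T2−T1)−(T1−T0) = T2−2T1+T0.
- **Time.** "Timepoint will be included as a categorical within-subject variable with four levels", that is, by assessment number T0 to T3. No term for calendar date, season or period is named.
- **Cohort.** Because recruitment is staged, "cohort will be included as a fixed-effect covariate to account for cohort-related differences over time (e.g., staff changes or evolving site practices").
- **Interactions.** "Fixed effects will be estimated for timepoint, tDCS condition, centre, cohort, and their relevant interactions". Cohort × timepoint is not named, but may be meant.
- **Random part.** "Models will include a random intercept for baseline differences across individuals", with a random slope for timepoint where the data support it.
- **Layout.** Under Trial design there are "five cohorts, each comprising approximately 20–24 participants, spaced 16–20 weeks apart". Every participant waits 16 weeks, is then treated for 16–20 weeks, and has T2 within 2 weeks of the end of treatment.

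**The concern.** Randomisation is only between active and sham tDCS. The CR question is answered within persons, with the wait always before the treatment. Whatever changes with the calendar between a participant's wait and treatment (season, staff, site practice) is therefore a rival explanation for the CR estimate.

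The plan names two such changes and assigns them to the cohort covariate. If that term does nothing to the contrast, the trial report could state that staff and practice changes were adjusted for when they were not. This goes beyond detail left to an analysis plan, because the article gives a specific term a task it cannot perform.

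**Working it through.** The plan gives no figure for calendar effects, so there is none to reproduce. The check is algebra, followed by illustrations under stated assumptions.

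**1. The cohort main effect.** A participant in cohort k carries the same effect g at every visit. In T2−2T1+T0 it contributes g − 2g + g = 0. In simulated data with complete visits, adding the cohort term changed the contrast by less than 1e-14. With 20% monotone dropout the change was at most 0.004 SD.

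**2. Cohort × timepoint.** This lets the contrast differ between cohorts. Averaged over equal-sized cohorts it is the same number (agreement to about 14 decimals). Within a cohort, calendar date remains tied to visit, so nothing calendar-related is separated out.

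**3. Standard error.** Assume an exchangeable correlation of 0.6 and 5 × 20 = 100 completers. Then Var(T2−2T1+T0) = 6(1−0.6) = 2.4, the SD is 1.549, and the SE is 1.549/√100 = 0.155 outcome SD. It is 0.1549 both without and with the cohort term.

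**4. A yearly cycle of amplitude A (assumed).** Let ω = 2π/52, spacing s = 16–20 weeks, and T1–T2 interval L = 16–22 weeks (16–20 of treatment plus up to 2).

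- Single-cohort factor: |1 − 2e^(16iω) + e^((16+L)iω)| = 2.71 at L = 16 and 3.27 at L = 22.
- Averaging factor over five cohorts: |sin(5ωs/2) / (5 sin(ωs/2))| = 0.241 at s = 16, 0.169 at s = 18 and 0.051 at s = 20.

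Worst-phase bias in the pooled contrast is the product of the two:

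| Spacing | L = 16 | L = 22 |
|---|---|---|
| 16 weeks | 0.65A | 0.79A |
| 18 weeks | 0.46A | 0.55A |
| 20 weeks | 0.14A | 0.17A |

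The values are the same with and without the cohort term.

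**5. A lasting 0.3 SD step common to all sites (assumed).** A cohort in treatment when the step occurs contributes +0.3, and a cohort waiting contributes −0.3.

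- If only the first cohort is waiting: −0.3/5 = −0.06.
- If one cohort is in treatment and the next is waiting: 0.
- If only the last cohort is in treatment: +0.06.
- If two cohorts are in treatment and none is waiting, which happens in schedules where T1–T2 exceeds the spacing: 0.6/5 = +0.12.

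The range is −0.06 to +0.12 SD. For T1–T2 of 16–20 weeks, the bias is zero for about 43–67% of possible calendar weeks.

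**6. Possible adjustments (same 100 completers, correlation 0.6).**

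- *Annual sine and cosine in assessment date, with cohort and timepoint.* The contrast stays estimable and an annual sinusoid is removed. The SE is at most 0.161, and 0.161/0.155 is about 4% larger.
- *16-week calendar bins, all intervals exactly 16 weeks.* Leakage is zero and the SE is 0.165 (+6%).
- *16-week bins, spacing 20, L = 16.* The SE rises 13–21%, and worst-phase seasonal leakage grows from 0.14A to 0.25A–0.47A, depending on where the bins start.
- *16-week bins shifted 8 weeks, spacing 18, L = 20.* The SE rises 43%, and the largest step bias goes from 0.12 to 0.30 SD. The worst schedule run cost 83% in SE.

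**The case against.** **The sentence may mean only differences between cohorts enrolled at different times.** A cohort fixed effect does adjust those. This reading is possible, but the sentence speaks of differences over time and gives staff changes and evolving practice as examples. A reader will take these as handled in the primary comparison, so the wording needs correcting on either reading.

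**A sensitivity analysis may be left to an analysis plan that is not shown.** This is fair: its absence alone would be no finding. What stands is the incorrect purpose given to the cohort term.

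**Several stronger readings are tempting, and the documents do not support them.**

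- *The plan makes no use of its concurrent cohorts.* Pooling the staggered cohorts already cancels much of a common disturbance, often all of a single step.
- *Season could account for 22% of the planned effect.* That figure takes an assumed A of 0.1 SD at the least favourable spacing and phase, and divides 0.079 outcome SD by d = 0.36. The sample size section uses d in a paired t-test, so it is probably in SDs of the difference. At correlation 0.6, 0.36 × 1.549 = 0.558 outcome SD, and 0.079/0.558 is about 14%. At 20-week spacing the bias is only 0.014–0.017 SD. No document gives evidence of seasonality in ILSS or GAS.
- *Calendar time is the main rival explanation.* The documents do not rank it above repeated testing or expectancy, and the Discussion already acknowledges the lack of a separate control group as a limitation.
- *Calendar bins remove the problem for 6%.* This holds only if visits line up exactly, which the stated spacing and treatment lengths do not ensure.

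**Conclusion.** The point holds as a matter of algebra. The cohort term adjusts level differences between cohorts and has no effect on the primary CR contrast with complete data; the effect under dropout is negligible. Cohort × timepoint does not change this.

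The size of what remains is unknown and may be small. The seasonal and step figures rest on assumed amplitudes, a pure 52-week sinusoid, a step common to all sites, equal cohort sizes and a 16-week wait. The standard errors further assume 100 completers and correlation 0.6. Exposure to season is modest at 20-week spacing and clearly larger at 16-week spacing.

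The statement should be corrected because it concerns the primary before-after estimate and claims a protection that the model does not give. It does not show that the CR estimate will be materially biased.

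**What to change.** 1. **Reword the cohort sentence.** State that the cohort term adjusts only for level differences between cohorts and does not protect the CR contrast from calendar change. Say which interactions are meant.
2. **Prespecify one sensitivity analysis of the CR contrast for ILSS-SR and the informant ILSS.** Adjust for calendar using actual assessment dates, for example with annual sine and cosine terms next to timepoint and cohort. The cost is two model terms and an SE up to 4% larger in that analysis, under the assumptions above. It needs the date of each assessment, which I assume is recorded.
3. **Use fixed calendar bins only if the realised visit dates line up across cohorts.** Misaligned bins cost 13% or more in SE in several schedules and can increase bias.

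The limits should be stated with the analysis. Season terms do not remove a step change. A common calendar term does not remove a change at one of the three centres. The adjustment does not apply to GAS if GAS has no T0 score: Table 1 shows goals set at T0 and first rated at T1, so T2−2T1+T0 may not exist for that outcome.

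Recruitment is ongoing, so both changes can be made before the outcomes are analysed.

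### The random slope on categorical timepoint is not identifiable for continuous outcomes with one record per visit, so the plan leaves the working covariance model to be chosen after the data are seen

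*Protocol article*

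**What the plan says.** The Statistical analysis section plans "multilevel models implemented in R (‘lme4’ or ‘glmer’ packages"), with a separate model for each outcome. On the time variable it says: "Timepoint will be included as a categorical within-subject variable with four levels". On the random part: "Models will include a random intercept for baseline differences across individuals, and, where supported, a random slope for timepoint"; the sentence continues that "a random slope for timepoint will allow individual trajectories over time (simplified if convergence issues arise"). On estimation: "Models will be estimated using maximum likelihood". On contrasts: "We will set T1 (pre-intervention) as the reference level", and the primary effect of cognitive remediation (CR) is judged by "comparing changes observed during the intervention period with changes during the waitlist period, pooling across tDCS conditions".

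Table 1 (Participant timeline) shows each repeated outcome assessed once at each of T0, T1, T2 and T3. The exception is GAS, whose goals are set at T0 and rated at T1, T2 and T3. No residual covariance structure, order of simplification or robust standard error is stated.

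**The concern.** A random slope on a factor is a set of random effects, one for each non-reference level. With a random intercept and four levels that makes four random effects per person, and a person contributes at most four values. The residual variance then has nothing left to be estimated from. The obstacle comes from the visit schedule. It is not a numerical accident that may strike one outcome and spare another, so non-convergence is the wrong trigger for it.

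Two things are at stake. First, the analyst will have to pick another covariance model once the data are in hand, possibly outcome by outcome, in a trial that controls family-wise error over three primary outcomes. Second, the easiest retreat is to the random intercept alone. That model assumes equal variance at all visits and equal correlation between every pair, although the gaps are about 16 weeks, 16 to 22 weeks and six months, and treatment falls in the second. If the assumption fails, the standard errors of the key contrasts are off, in different directions for different contrasts. With 20% dropout expected, the covariance model also affects the estimates themselves, because likelihood methods use it to borrow information across missing visits.

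**Working it through.** The plan gives no figure on this point, so there is none to reproduce.

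**Inputs from the article.** Four-level factor, random intercept and slope, lme4, T1 as reference (Statistical analysis); one record per visit, three rated values for GAS (Table 1). Visit times are approximated from Trial design as 0, 16, 34 and 60 weeks: a 16-week wait, 16 to 20 weeks of treatment with T2 within two weeks after it, then six months taken as 26 weeks. **Assumed:** all variances and correlations.

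**1. Parameter count.** Intercept plus three slopes: 4 variances + 6 covariances + 1 residual variance = 11 parameters. A 4 × 4 covariance matrix has 4 × 5 / 2 = 10 distinct elements. The Jacobian of the marginal covariance has rank 10, so one parameter is not identified. For GAS: 3 + 3 + 1 = 7 parameters against 3 × 4 / 2 = 6 elements; rank 6.

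**2. Fit.** On simulated data for 100 people at four visits, `lmer` with `(timepoint | id)` stopped with an error: 400 observations against 400 random effects. With that check switched off, the model did return fixed effects and standard errors, because its marginal covariance is simply an unstructured 4 × 4 matrix. Only the split between random effects and residual is undetermined.

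**3. Simpler slopes are identifiable.** Linear time, 4 of 4 parameters; a dummy for the period after T1, 4 of 4; correlated T2 and T3 dummies, 7 of 7; uncorrelated dummies, 5 of 5.

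**4. If only the random intercept is kept.** With T1 as reference, the primary contrast is (T2 − T1) − (T1 − T0) = T2 − 2·T1 + T0, so c = (1, −2, 1, 0) for (T0, T1, T2, T3). For complete data, omitting the common factor 1/n:

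- true variance: c′Σc
- variance the model reports: c′c × trace(PΣ)/3, with P = I − J/4
- SE ratio = √(reported / true); type I error ≈ 2Φ(−1.96 × ratio)

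*Worked case: AR(1), 0.7 between adjacent visits, unit variances.* Correlations at lags 1, 2, 3 are 0.7, 0.49, 0.343. Their mean over the six pairs is (3 × 0.7 + 2 × 0.49 + 0.343)/6 = 0.5705, so the model's residual variance is 1 − 0.5705 = 0.4295.

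- Primary contrast: true 6 − 4(0.7) − 4(0.7) + 2(0.49) = 1.38; reported 6 × 0.4295 = 2.58; ratio √(2.58/1.38) = 1.37, so the SE is 37% too large.
- T3 − T1: true 2 − 2(0.49) = 1.02; reported 2 × 0.4295 = 0.86; ratio √(0.86/1.02) = 0.92, so the SE is 8% too small; type I error about 7.2%.

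*Other assumed covariances, with the visit times above (SE ratios):*

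| Assumed covariance | T2 − 2·T1 + T0 | T2 − T1 | T3 − T1 |
|---|---|---|---|
| Compound symmetry, correlation 0.6 | 1.00 | 1.00 | 1.00 |
| Decaying correlation, 0.6 to 0.9 per 16 weeks | 1.35 to 1.60 | 1.18 to 1.31 | 0.90 to 0.87 |
| Random linear trend, slope variance 0.02 to 0.05 | 1.06 to 1.15 | 1.05 to 1.11 | 0.97 to 0.95 |
| Extra variance 0.1 to 0.3 shared by T2 and T3 | 1.02 to 1.05 | 0.98 to 0.95 | 0.98 to 0.95 |

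The smallest T3 − T1 ratio, 0.87, corresponds to a type I error of 8.7%. GAS has no rated T0 value, so the primary-contrast column applies to the ILSS scores and not to GAS.

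**The case against.** The strongest reply is that the text is already conditional: the slope enters only if supported and may be simplified. A reader might infer that every model must therefore collapse to a random intercept. The article does not say so. Step 3 shows simpler slopes that the same software can fit, and an analyst could choose one of them. This part of the reply stands.

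A reader might also infer that the standard errors will be wrong. That too goes beyond the document. They are exact under compound symmetry and only slightly off under several of the covariances tried. The large errors need correlation that decays with time and no stable person component, which is debatable in people with long-standing disability. In every case tried, the primary contrast was correct or conservative, so no false claim for CR follows. The inflation mainly affects T3 vs T1, with a smaller amount for T2 vs T1 in one scenario; the T1-to-T3 stimulation comparison is expressly hypothesis-generating. Turning the 37% into a loss of power would require reading d = 0.36 as raw standard deviation units of the double difference, which the sample-size section does not say, so no power figure is given here.

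Nor does the problem reach every model. A `glmer` model for counts or binary data has no free residual variance, and the Behapp data may have several records per 14-day phase.

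Finally, covariance details are commonly left to an analysis plan, which is not shown. That would answer an omission. Here the article states a particular structure, and it is one that the named software rejects for single-record continuous outcomes, including the three primary outcomes if they are analysed as continuous scores.

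**Conclusion.** The point holds for continuous outcomes with one record per visit. The random slope as described is structurally unidentifiable, lme4 refuses it by default, and the stated conditions leave its replacement open until the data are seen. That part needs no assumption beyond the visit schedule.

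The effect on inference is conditional. If the random intercept alone is kept, the ILSS primary contrast has a standard error between correct and about 60% too large, and T3 vs T1 between correct and about 13% too small. Both ranges assume complete data, the approximate visit times and the covariances listed. The likely harm to the primary analysis is lost precision, not a spurious effect. It is worth correcting because a better model is available at almost no cost, but it does not undermine the design.

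**What to change.** For continuous outcomes, drop the random slope and fit an unstructured covariance across the scheduled visits, using `mmrm`, or `nlme::gls` with `corSymm` and `varIdent`. Use REML with Kenward-Roger or Satterthwaite degrees of freedom. This gives the same marginal covariance that the full categorical slope would imply, without the unidentifiable split.

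With T1 as reference, test the primary effect as coefficient(T2) + coefficient(T0), averaged over the two stimulation arms, wherever a T0 value exists. For GAS, use the unstructured matrix over its three rated visits and state separately which contrast represents the CR effect.

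Keep `glmer` for non-Gaussian outcomes, with an identifiable random-effects structure named in advance. If the authors prefer to stay with lme4 throughout, they should fix an ordered list of identifiable simplifications before unblinding.

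The cost is a change of wording and of R function, and a few more covariance parameters: ten for four visits and six for GAS, against two for a random intercept with residual. The planned sample supports that comfortably. Recruitment was still under way at submission, so the change can be made before any outcome analysis.
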